## Abstract

Participants will be recruited from the Faculty of Physical Education and randomly assigned to either the hamstring stretching group or the control group with education only. The primary outcome measures will be pain intensity, musculoskeletal discomfort, and functional disability. Secondary outcome measures will be satisfaction with the intervention and flexibility of the hamstring. A total of 44 participants fulfilling the inclusion criteria will complete the study. As an increase in LBP frequency is observed, it seems justified to determine effective interventions for LBP and musculoskeletal discomfort in young people. The findings of this study will provide information about the effect of an 8-week intervention involving active hamstring flexibility exercises with hip flexion mobilization on the reduction of LBP and musculoskeletal discomfort during prolonged sitting in young adults. We hope this study will add to the development of ergonomic recommendations for young people with LBP.

## 1. Introduction

Decreased flexibility of muscles, poor posture, prolonged sitting, fatigue resulting in soft tissue exertion, lumbosacral overload, and increased muscle fiber tone lead to an imbalance in lumbopelvic rhythm [1,2,3]. Four muscle groups support the pelvis and keep it in its natural position, including the erector spinae, hamstrings, gluteus maximus, abdominals, and hip flexors [4,5]. Weakening of central stabilization forces the musculoskeletal system to activate other stabilization mechanisms in areas distant from the spine, such as hyperactivity of the hamstrings [1,6].

Restricted lower extremity muscle flexibility, including in the hamstring, iliopsoas, and quadriceps, and limited range of motion of the hip joint, might be risk factors for low back pain, LBP [7]. LBP is defined as pain in the posterior part of the body from the lower margin of the 12th ribs to the lower gluteal folds, without pain referred to one or both lower limbs, and lasting for at least 1 day [8]. LBP can be specific or non-specific. Specific pain is pain caused by a certain disease or structural problem in the spine, or pain radiating from another part of the body due to underlying conditions such as spondylolisthesis, stenosis, malignancy, or inflammatory processes [9]. We are interested in non-specific pain, which is pain that cannot be explained with reference to a specific disease or structural problem. The prevalence of LBP has increased significantly over the last twenty years, especially among young people [8].

Muscle flexibility is essential in sports and physical fitness [10]. The length of the hamstring influences the motion of the pelvis during hip movements, consequently influencing the angle of lumbar lordosis [11,12,13]. In most daily and sporting activities, the hamstring muscles are active, and that is why it is necessary to maintain their normal length. Hamstring stretching should create an opportunity to practice movement and develop correct spinal patterns during hip flexion and extension. Maintaining neutral spinal curvature during activities is one of the basic principles of protecting the lumbar spine [14].

In individuals with LBP, decreased flexibility of muscles is associated with low back pain [15,16,17,18]. Stretching exercises are important in preventing and treating LBP [3,19]. One important option is the adoption of an exercise protocol that combines active hamstring stretching with hip flexion mobilization and the development of the habit of correct hip flexion, protecting the lumbar spine. Existing treatments for LBP often focus on general flexibility and strengthening exercises without targeting specific muscle groups such as the hamstrings, in conjunction with hip flexion techniques. This study addresses this gap by proposing a targeted intervention that may offer a more effective approach to managing LBP and discomfort in young adults, a demographic increasingly affected by sedentary lifestyles and prolonged sitting.

This is a protocol of a study that would evaluate the effectiveness of 8 weeks of active hamstring stretching exercises combined with hip flexion mobilization in reducing LBP and perceived musculoskeletal discomfort during prolonged sitting in young adults. 

## 2. Methods

### 2.1. Study Setting and Design

This will be a single-blind randomized controlled trial. The study protocol has been approved by the Senate Commission of Research Studies Ethics Józef Piłsudski University of Physical Education in Warsaw [SKE 01-05/2023], and the study has been prospectively registered at ClinicalTrials.gov [NCT05995145]. The protocol was prepared according to the Standard Protocol Items: Recommendations for Interventional Trials (SPIRIT) guidelines [20] and complies with the latest version of the Helsinki Declaration [21]. Written informed consent for participation will be obtained from all the participants involved in the study. The study will be conducted at the Faculty of Physical Education and Health, Jozef Pilsudski University of Physical Education in Warsaw, Biala Podlaska, Poland. The Consolidated Standards of Reporting Trials (CONSORT 2010) statement will be followed for the reporting of this study [22]. 

### 2.2. Study Population

The participants will be recruited according to the following inclusion criteria: (1) students of physical education; (2) age 18–25 years (18–25 years old); (3) with non-specific LBP; (4) with pain that has lasted at least 3 months; (5) without a history of spinal surgery; (6) no hamstring stretching exercises in the last 6 months; and (7) with hamstring muscle tightness.

The exclusion criteria are as follows: (1) specific LBP; (2) other criteria preventing participants from adequate participation in the study, such as pregnancyor menstrual pain; (3) leg length discrepancy over 1 cm; (4) previous spinal surgery; (5) presence of any contraindication to exercise; or (6) medically verified chronic back disorders.

### 2.3. Sample Size

The necessary minimum total number of subjects (n = 44) was obtained using the G*power program assuming a medium-sized effect (d = 0.50) at a significance level of 0.05 and a statistical power of 0.85. The sample will be increased by 10% to compensate for possible dropouts (overall sample = 48 participants). 

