### 2.4. Randomization

Eligible participants will be randomly assigned to one of two groups: the experimental group (education, hamstring stretching, core stabilization, hip flexion mobilization) or the control group (education without any specific exercises). The randomization will be carried out by a researcher external to the study using a Microsoft Excel software random number generator before the beginning of the main study. Concealed allocation will be achieved using opaque envelopes. After the baseline assessment, the researcher responsible for the intervention will open the envelope to identify the group to which the participant will be allocated.

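### The 85% power stated for 44 participants at d = 0.50 does not hold for the randomized two-arm comparison; under ordinary assumptions it is about 37%

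*Protocol article*

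**What the plan says.** Section 2.3 (Sample Size) states: "The necessary minimum total number of subjects (n = 44) was obtained using the G*power program". The inputs that it gives for this calculation are a standardized effect, an error rate and a target power, in these words: "assuming a medium-sized effect (d = 0.50) at a significance level of 0.05 and a statistical power of 0.85". On attrition it adds: "The sample will be increased by 10% to compensate for possible dropouts (overall sample = 48 participants"). The Abstract treats 44 as the number of completers: "A total of 44 participants fulfilling the inclusion criteria will complete the study".

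Section 2.4 (Randomization) sets the design: "Eligible participants will be randomly assigned to one of two groups", an exercise group and an education-only control group. Section 2.9 places the self-reported primary measures at baseline and after 8 weeks. Section 2.13 (Data Analysis) plans a Mann–Whitney U test between groups and a mixed-design ANOVA with intervention and time as factors. Section 2.3 does not say which of these the calculation refers to.

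**The concern.** Section 2.3 gives effect size, significance level, power and total sample size together, so the last can be checked against the other three. For two independent groups, d = 0.50 is a modest effect that usually needs well over 100 participants at 85% power. A total of 44 is about 30% of the two-sided requirement (44/146 = 0.30).

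What is at stake is the interpretation of the result. If a true between-arm difference of d = 0.50 has a 37% chance of reaching significance, it is missed about 63% of the time. A non-significant result read against a stated power of 85% would look like fair evidence against a medium effect, and it would not be. The Discussion acknowledges the small sample only for generalizability and for sex-specific analyses, not for power on the main comparison.

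**Working it through.** **Inputs.** From Section 2.3: d = 0.50, alpha 0.05, power 0.85, total 44 (48 with the dropout allowance). From Section 2.4: two arms. Assumed, because the article does not say: 1:1 allocation (22 per arm) and a two-sided test; one-sided results are also shown.

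**1. Attempt to reproduce 44 for two independent arms.** For a two-sample t-test with n per arm, power comes from the noncentral t distribution with df = 2n − 2 and noncentrality d·√(n/2). The smallest n with power of at least 0.85 at d = 0.50 is:

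- two-sided: n = 73 (power 0.851; n = 72 gives 0.846), total 146;
- one-sided: n = 59 (power 0.854; n = 58 gives 0.849), total 118.

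The stated 44 is not reproduced.

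**2. Power with the stated sample.**

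- 22 per arm: noncentrality 0.50 × √11 = 1.658, df = 42. Power is 36.7% two-sided and 49.5% one-sided.
- 24 per arm (all 48 retained): 39.6% two-sided.
- Mann–Whitney U with normal data: relative efficiency 0.955 gives an effective 22 × 0.955 = 21.0 per arm and power of about 35%. A simulation of 100,000 trials also gave 35%.

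**3. Detectable effect at 85% power, 22 per arm.** d = 0.92 two-sided, 0.82 one-sided.

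**4. The planned group-by-time interaction.** With two time points this is a two-sample test on change scores. If the between-group difference is 0.50 outcome SDs and the baseline-to-week-8 correlation is ρ, the SD of change is √(2(1 − ρ)), and the effect on the change scale is 0.50/√(2(1 − ρ)).

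| ρ | SD of change | Effect on change scale | Power, 22 per arm | Detectable d at 85% |
|---|---|---|---|---|
| 0.3 | 1.183 | 0.423 | 28% | 1.09 |
| 0.5 | 1.000 | 0.500 | 37% | 0.92 |
| 0.7 | 0.775 | 0.645 | 55% | 0.72 |
| 0.8 | 0.632 | 0.791 | 73% | 0.58 |
| 0.85 | 0.548 | 0.913 | 84% | 0.51 |

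The correlation needed for 85% is 1 − (0.50/0.9248)²/2 = 0.854.

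**5. Calculations that do return 44.**

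- *Matched-pairs Wilcoxon signed-rank test, d = 0.50, two-sided, minimum relative efficiency 0.864.* The effective n is 44 × 0.864 = 38.0, with power 0.851; 43 gives 0.843. So 44 is exactly the answer, but for a pre-post change in a single sample.
- *Repeated-measures within-between interaction, f = 0.25.* The noncentrality is f²·N·2/(1 − ρ). At ρ = 0.42 and N = 44 it is 0.0625 × 44 × 2/0.58 = 9.48, with power 0.853. At ρ = 0.5 the routine returns 38, and N = 44 has power 0.90. For a group difference in change of δ SDs, the same noncentrality is δ²N/(8(1 − ρ)). Equating the two gives δ = 4f = 1.0. So f = 0.25 here means a 1.0 SD group difference in change, twice a between-group d of 0.50.

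**The case against.** The strongest reply is that 44 may be the correct output of a legitimate G*Power routine. That stands. The matched-pairs Wilcoxon route uses all three inputs stated in Section 2.3 unchanged and adds only a relative-efficiency setting, and the plan does use rank-based methods. The f = 0.25 interaction also gives 44 at a plausible correlation. A reader might infer that 44 is an arithmetic slip that no standard routine would produce. The documents do not support that: which routine was used cannot be told from Section 2.3. But neither route gives 85% power for a between-arm difference of d = 0.50, which is the comparison that randomization serves.

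A second reply is that a journal article may leave the test, sidedness and correlation to a fuller document. That is fair, and their absence is not counted here as a separate defect. The point rests on figures the article does state.

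A third is that using the baseline measurement raises power. It does when the correlation exceeds 0.5, as the table shows, but 85% needs about 0.85. Analysis of covariance would do somewhat better (46% at correlation 0.5, 62% at 0.7), but Section 2.13 does not plan it.

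Finally, nothing in the article says that a null result will be read as absence of effect. That consequence is a risk, not a stated intention.

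**Conclusion.** The point holds as a mismatch between the power stated in Section 2.3 and the two-arm design. For a between-group d of 0.50, 44 completers give about 37% power two-sided (about 35% by Mann–Whitney with normal data, 49% one-sided), against the 85% stated. The matching sample size is 146 two-sided or 118 one-sided.

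The 37% and the detectable d of 0.92 assume 1:1 allocation, a two-sided test and 44 completers, with either an unadjusted comparison or the interaction at correlation 0.5. A reader might infer that the trial can only ever detect d of about 0.92. That is too absolute: at correlation 0.7 the planned interaction detects about 0.72. The finding that 85% is not reached at d = 0.50 holds for one-sided testing, for all 48 retained, and for the interaction at correlations up to about 0.85.

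This should be corrected before results are reported, because the stated power is more than twice what the design delivers under these assumptions.

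**What to change.** Keep the sample size and correct Section 2.3. Name the outcome, the test, the sidedness and the assumed baseline-to-week-8 correlation, and replace the power statement with, for example:

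> With 44 completers (22 per arm, 1:1), the trial has 85% power at two-sided alpha 0.05 to detect a between-group difference of about d = 0.92 (unadjusted comparison, or group-by-time interaction at pre-post correlation 0.5; about 0.72 at correlation 0.7). Power for d = 0.50 is about 37% (55% at correlation 0.7).

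Add that a non-significant result will be interpreted from the confidence interval for the between-group difference, not as absence of effect. Quote power for analysis of covariance only if that analysis is adopted in Section 2.13.

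The cost is wording: no extra participants and no change to the conduct of the trial. The downside is that the stated power becomes less favourable.

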### 2.4. Randomization

Eligible participants will be randomly assigned to one of two groups: the experimental group (education, hamstring stretching, core stabilization, hip flexion mobilization) or the control group (education without any specific exercises). The randomization will be carried out by a researcher external to the study using a Microsoft Excel software random number generator before the beginning of the main study. Concealed allocation will be achieved using opaque envelopes. After the baseline assessment, the researcher responsible for the intervention will open the envelope to identify the group to which the participant will be allocated.

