### 2.8. Pre-Intervention Data Collection Sheet 

Before random group assignment, participants will receive the survey containing questions about age, gender, current physical activity (number of training days and hours per week, sports discipline), history of illnesses, injuries, surgeries due to spinal ailments, LBP physiotherapy and confirmed by which medical doctor, and body posture defects. A questionnaire will also be used to collect data about the experience of LBP within the last three months. Individuals who respond positively (“yes”) to the question “Have you experienced low back pain for the last three months?” will answer the question on the frequency of LBP (rarely, a few times per week, often, or constantly) and the types of situations in which LBP occurred, increased, or worsened.

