### 2.12. Timeline of the Study

We designed the timeline of the study using the SPIRIT framework (Table 1). At enrollment, the purpose of the study and research procedures will be explained to the participants. The pre-screening will address the specific inclusion and exclusion criteria for the study, basic demographic data, and the frequency of LBP. Participants who meet the inclusion criteria will be invited to attend a baseline assessment (Table 2). All the tests will be performed during morning hours in the laboratory. 

At the baseline assessment session, participants will be requested to complete the VAS, ODI, and Borg CR-10 scale. After completion of the baseline assessment, participants will be randomly assigned to one of two groups (experimental or control), and simultaneous implementation of the exercise program will commence. After 8 weeks, all assessment measures for all participants will be repeated in the same way as the baseline measurements (Table 2).

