We are aware that the protocol relies on self-reported measures for pain intensity, functional disability, and musculoskeletal discomfort, which may be subject to bias. Future studies should incorporate objective assessments such as electromyography (EMG) to measure muscle activity and flexibility more precisely. This tool can provide more accurate and reliable data on the physiological effects of the intervention. 

The study does not account for potential differences in response to the intervention between males and females. Gender-specific analyses cannot be performed due to the small sample size. In the future, we plan to perform gender-specific analyses to understand how males and females might respond differently to the intervention and tailor future protocols accordingly.

Future research should include a larger sample size to enable stratified analyses and explore potential gender differences. We are aware of this limitation in terms of the internal validity of our study [33]. In addition, with a total of 48 participants, the study’s findings may not be generalizable to the broader population of young adults with LBP. Larger-scale studies and long-term follow-up assessments are needed to confirm the results, enhance the generalizability of the findings, and explore the effects of the intervention across different populations, including various age groups and individuals with different levels of physical activity. 

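### As described, sex enters neither the allocation (2.4) nor the outcome model (2.13), although it is recorded before assignment; stratifying by sex would cost almost nothing and mainly helps the outcomes measured only after treatment

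*Protocol article*

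**What the plan says.** - **Allocation (2.4).** "Eligible participants will be randomly assigned to one of two groups". An external researcher generates the allocation "using a Microsoft Excel software random number generator before the beginning of the main study". Opaque envelopes conceal it, and the researcher who delivers the intervention opens the envelope after the baseline assessment. No ratio, arm size, block or stratum is named, and none is ruled out.
- **Sex is known in time (2.8).** Before assignment, "participants will receive the survey containing questions about age, gender, current physical activity".
- **Model (2.13).** The mixed-design ANOVA has two factors, intervention and time. Mann–Whitney and chi-square tests are also listed. No sex term appears.
- **Discussion.** "The study does not account for potential differences in response to the intervention between males and females". Sex-specific analyses are said to be impossible at this sample size, and stratified analyses are left to larger studies.
- **Schedule (2.9, Table 2).** Pain, disability and discomfort are measured at baseline and after 8 weeks. Flexibility and global perceived improvement are scheduled only after the intervention.
- **Size (2.3).** "The sample will be increased by 10% to compensate for possible dropouts (overall sample = 48 participants").

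**The concern.** The Discussion attributes the limits on handling sex to the small sample. That holds for testing whether men and women respond differently. It does not hold for balancing sex at allocation or adjusting for it in the model, and both are feasible with 48 participants. The plan as described uses neither, so chance alone decides how men and women fall between the arms.

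An imbalance matters where sex is related to the outcome and the analysis has no baseline value to absorb it. On the published schedule, that applies to hamstring flexibility and global perceived effect. A reader of the finished trial who saw clearly different proportions of women in the two arms would find those two results harder to trust.

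**Working it through.** **Inputs.** N = 48 (2.3). Two arms (2.4), with 1:1 assumed because no ratio is stated. Simple randomisation is also assumed. The proportion of women is not in the document; about 30% (14 of 48) and 50% (24 of 48) are assumed.

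**The plan's own figure.** 44 × 1.10 = 48.4, against the stated 48. The figure of 44 does not follow from d = 0.50, alpha 0.05 and power 0.85 in an independent two-sample t-test, which needs 146 two-sided. That is a separate matter, and nothing below depends on it.

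**Arm sizes.** With n1 ~ Binomial(48, 0.5):

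| Event | Probability |
|---|---|
| exactly 24/24 | 11.5% |
| differ by 6 or more (21/27) | 47.1% |
| differ by 8 or more (20/28) | 31.2% |
| differ by 12 or more (18/30) | 11.1% |

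Information relative to equal arms is 4·n1·n2/N²:
- 20/28: 4 × 20 × 28 / 2304 = 0.972, a loss of about 3%.
- 18/30: 4 × 18 × 30 / 2304 = 0.938, a loss of about 6%.

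For a two-sided t-test at d = 0.50, power is 39.6% at 24/24, 38.7% at 20/28 and 37.5% at 18/30. Unequal arm size is a minor matter.

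**Sex balance.** From 400,000 simulated allocations, the chance that the share of one sex differs between arms by 20 points or more is:

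| Assumed share | Simple | Fixed 24/24, no sex stratum |
|---|---|---|
| about 30% | 14.1% | 11.1% |
| 50% | 19.4% | 14.8% |

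The standard deviation of the imbalance barely moves when the arms are fixed at 24/24: 0.134 against 0.133 at about 30%, and 0.147 against 0.146 at 50%. Equal arms alone do not balance sex. Only a sex stratum does.

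**Effect on the comparison.** Let p1 and p0 be the proportions of women in the two arms, and let δ be the sex difference in the outcome.
- Single post-treatment value: the arm difference shifts by (p1 − p0)·δ(post).
- Change from baseline: the shift is (p1 − p0)·[δ(post) − δ(pre)]. This is zero if the sex difference is stable over time.

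The group-by-time test therefore removes a constant sex difference for pain, disability and discomfort. A comparison of 8-week values alone would not.

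For flexibility, assume δ = 0.3 to 0.8 SD (no source in the document). A 20-point imbalance then shifts the arm difference by 0.20 × 0.3 = 0.06 SD to 0.20 × 0.8 = 0.16 SD. Set against the planned d = 0.50, that is 12% to 32%. Set against the standard error at 24/24, √(1/24 + 1/24) = 0.289 SD, it is about 0.2 to 0.55 standard errors. The SD scale does not transfer directly to the dichotomised global perceived effect, but the same logic applies if sex is related to that rating.

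**The case against.** The strongest objection is that the point leans on silence. Excel can shuffle 48 fixed slots into 24/24 or produce a blocked list, and a journal article may leave such detail to the full protocol. This stands as a limit: a reader might infer that allocation is unrestricted, but the article does not say so, and every probability above is conditional on it. It does not dispose of the point. The model in 2.13 is stated positively with two factors, and the Discussion itself raises sex and defers stratified analyses.

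Other stronger readings are tempting but not supported:
- **Sex is declared out of reach.** The Discussion rules out sex-specific analyses and raises sex as a possible modifier of response. It does not say that sex cannot be balanced or adjusted for.
- **A list made in advance cannot use sex.** It can, with one list and one envelope set per sex.
- **The whole cohort is allocated in one step.** Section 2.12 says that "simultaneous implementation of the exercise program will commence", but this may mean only that both arms run in parallel, and 2.4 describes an envelope opened for the individual participant.
- **The comparison is biased.** Chance imbalance averages out over randomisations and is already reflected in the standard error of an unadjusted comparison.

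It can also be said that entry requires hamstring tightness (2.2), defined in 2.11 as a straight leg raise of 70° or less. That narrows baseline differences in flexibility. Moreover, 2.12 speaks of repeating all measures as at baseline. If a pre-treatment value is in fact recorded, much of the exposure for flexibility goes. As 2.9 and Table 2 stand, it is not scheduled. Finally, simple randomisation is valid, and stratification is a choice. That is true, and it is why this is an inexpensive improvement and not a flaw that threatens the trial.

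**Conclusion.** The point holds in a limited form. As described, sex is used in neither allocation nor analysis although it is known before assignment, and the small sample does not explain this.

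Under simple 1:1 allocation of 48, arms differing by 8 or more are common (about 31%) but cheap. A sex imbalance of 20 points or more arises in about 14–19% of lists, assuming 30–50% women. The consequence is lost precision and credibility for the outcomes without a baseline (flexibility and global perceived effect). There is little effect on the group-by-time tests for pain, disability and discomfort unless sex also affects change. The shift of 0.06–0.16 SD rests on an assumed sex effect and describes only lists with a 20-point imbalance.

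**What to change.** - **2.4:** State a 1:1 ratio and the type of randomisation. Have the external researcher prepare the Excel lists separately for men and women, each with its own set of opaque envelopes. If students are allocated one by one, use blocks of random size within sex.
- **2.13:** Include sex as a factor in the between-group models, above all for flexibility and global perceived effect. For the dichotomised rating, a Mantel–Haenszel analysis stratified by sex can replace the plain chi-square test.
- **Discussion:** State that sex is balanced at allocation and adjusted for, but not tested as an effect modifier because the sample is too small for that.

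**Cost.** A few lines of text, the same spreadsheet and the same external researcher; one residual degree of freedom in a linear model (46 to 45 with 48 participants); no extra participants. With complete lists, balance within each sex is exact apart from an odd participant; blocks left unfinished at the end of recruitment leave a small residue. Small blocks make the end of a block somewhat easier to guess, since those delivering and receiving the intervention know the arm. Random block sizes reduce this, as does having the blinded assessor settle eligibility and baseline before the envelope is opened.
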